#### 2.7.3. Motor Task

In functional runs 2 and 3, participants will be instructed to perform motor actions similar to those observed in the action observation task. The conditions will include (a) execution with the right hand, (b) execution with the left hand, and (c) bimanual execution. A mixed block-event-related design will be used. Each block will contain four motor trials, separated by a 6 s interstimulus interval, during which the experimenter will present the next object. Trial blocks will be interspersed with rest periods, during which the participant will remain still, fixating on the experimental setup.

A metal-free, MR-compatible support will be placed above the participant’s hips to provide a stable surface for performing the actions. The apparatus will be positioned approximately 15 cm from the torso, ensuring that upper-body movement is minimized. Foam pads will be used to maintain arm position and prevent involuntary movements.

An experimenter will remain inside the scanner room throughout the acquisition to present the stimuli (i.e., the same belt-equipped objects used in the videos of the action observation task). Timing and condition instructions will be delivered to the experimenter through MR-compatible headphones. All motor actions will be video-recorded using an MR-compatible infrared camera (MRC hi-speed camera; 150 fps) to monitor task compliance.

#### 2.7.4. MRI Data Acquisition

Structural and functional images will be acquired using a 3T General Electric scanner (SIGNA Premier) equipped with a 48-channel head coil. Functional volumes will be collected during both the action observation and motor execution tasks using a gradient-echo echo-planar imaging (EPI) sequence. Acquisition parameters will be 52 axial slices, slice thickness = 2.5 mm, TR = 2000 ms, TE = 30 ms, FOV = 204 × 204 mm^2^, and flip angle = 75°.

In addition to functional images, anatomical scans will be acquired for lesion segmentation and image coregistration, including (a) a high-resolution 3D T1-weighted sequence and (b) a fast spin-echo (FSE) fluid-attenuated inversion recovery (FLAIR) sequence.

#### 2.7.5. Sample Size Estimation (fMRI Sample)

Sample size estimation for the present fMRI study was informed by BOLD signal changes reported in a previous study on children using an action observation paradigm (*N* = 10 per group) [36]. To our knowledge, no other randomized controlled trials have investigated children with diplegia or Cerebral Palsy with fMRI tasks involving action observation and execution. For the analysis, significant activation clusters within the Mirror Neuron System (including the ventral premotor cortex and the inferior parietal lobule) were considered, applying a statistical threshold of *p* < 0.001 with Family-Wise Error (FWE) correction for multiple comparisons at the cluster level. The power analysis conducted on these data (using the NeuroPower tool) indicated that, to detect significant BOLD changes (*p* < 0.05, Bonferroni corrected) with 80% power, a minimum of 6 participants per group would be required. To account for potential dropouts, the sample size was increased to 10 participants per group.

#### 2.7.6. Sampling for the fMRI Subgroup

All patients enrolled in the study protocol, both in the experimental and control groups, will be offered the opportunity to undergo the functional MRI (fMRI) examination before and after the treatment period. Participation in the fMRI study will be voluntary and subject to informed consent by the patients’ families. Only those who consent and meet the previously described eligibility criteria for MRI scanning will undergo the fMRI assessments. It is important to note that this does not constitute a separate sample; the fMRI subgroup will be composed exclusively of participants already included in the main protocol. To facilitate understanding of the procedure and reduce potential anxiety, families will receive detailed information through explanatory brochures, videos, and illustrated materials clearly describing the purpose, process, and experience of the fMRI exam.

### 2.8. Statistical Analyses

A descriptive statistical analysis (mean, standard deviation, and frequencies) will be conducted for both EG and CG. Initially, differences between the two groups at T0 will be examined for the various outcome variables, assessing the significance of the results through *p*-values. Depending on the data distribution, parametric or non-parametric tests will be applied. Subsequently, intergroup differences at the primary endpoint (T1) will be analysed. A second level of analysis will be performed to assess differences between follow-up and baseline evaluations. Additionally, Cohen’s d effect sizes and their 95% confidence intervals will be calculated to quantify the magnitude of the effects.

All clinical, neurophysiological, and technological data collected at baseline will be correlated with the outcomes to identify predictive markers of training response. Specifically, a two-stage procedure will be followed: (i) a LASSO-based variable selection method will identify the parameters most strongly associated with changes, and (ii) a statistical model will be developed based on the selected variables. The model will be quantified and optimized using cross-validation and bootstrap techniques.

The preprocessing of functional images will be performed using the SPM12 software, implementing routines for spatial realignment, slice-timing correction, anatomical-functional coregistration, segmentation, and normalization to the MNI template. Group-level statistical analyses will be conducted using the General Linear Model, which will be employed to calculate the main effects of experimental and control conditions (t-contrast). Subsequently, to assess the contribution of each experimental condition and activation differences for each subject, a Region of Interest (ROI) analysis will be performed in key areas of interest, extracting the BOLD signal associated with each condition. To evaluate the significance of BOLD signal differences within conditions (within-subject effects) and between groups (between-group effects), a Repeated Measures Analysis of Variance (rmANOVA) will be applied. All statistical parametric maps will be corrected for multiple comparisons using the Family-Wise Error (FWE) method.

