## 2. Materials and Methods

### 2.1. Study Design

The project is a non-profit two-arm exploratory randomized clinical study consisting of an experimental group and a control group. Recruitment, clinical experimentation, and analysis of all clinical, technological, and neuroimaging data will be carried out by the centres involved in the study: IRCCS Fondazione Stella Maris (Pisa), AUSL IRCCS of Reggio Emilia, University of Parma. The recruitment will be carried out by some staff members (who will not have access to the allocation sequence), which will be responsible for the identification of eligible children; then, a different group of staff members will take care of randomly assigning the enrolled children to the study groups.

After fulfilling the inclusion and exclusion criteria described below and obtaining signed informed consent, enrolled participants will undergo an initial baseline assessment (T0) and will be block-randomized (ratio 1:1) in the experimental group (EG) or the control group (CG), using a computer-generated set of random numbers by an independent operator. The EG will carry out an 8-week AOT period, while the CG will continue standard care; that is, they will continue their usual care without receiving any additional training (details in Section 2.5).

Families from both groups will be asked to complete a diary to track daily activities and therapies throughout all 8 weeks. After this period, both groups will be assessed again (T1). T1 will be the primary endpoint aimed at evaluating the short-term effects of AOT. All participants will also be evaluated at 8 and 24 weeks (T2 and T3, respectively) after T1 (Figure 1) to evaluate the medium- and long-term effects of AOT. Details of the AOT training and the adopted outcome measures are described below.

The clinical team asked the FTS foundation—an association composed of families of children with CP—for support in participant enrolment and involvement. They are actively participating in this study, particularly in awareness campaigns and participant enrolment. After the study’s completion, the FTS foundation will help the consortium involve families in reporting their experiences and be informed about the study results in a joined final event.

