### 2.6. Outcome Measures

Participants of both groups will undergo a series of tests commonly used in clinical practice, with a total duration of approximately 2 h. The evaluation will consist of clinical tests, questionnaires, and a technological part. All tests will be administered at all timepoints, unless otherwise specified. The evaluation will be structured as follows:

*Clinical assessment measures:*
Both Hands Assessment (BoHA [42]), identified as the primary outcome measure. It is an evaluation tool specifically designed to measure bimanual upper-limb performance in children with bilateral Cerebral Palsy.Melbourne Assessment 2 (MA2 [43]). It is a standardized tool designed to assess upper-limb movement quality in children with neurological impairments, aged between 2.5 and 15 years. It is carried out for each UL separately.Box and Block Test (BBT [44]). It is a quick and simple assessment tool for evaluating manual dexterity, with the two sides tested separately.

During these UL tests, participants will be required to wear Actigraphs on each wrist (described below).

Corsi Test [45]. This test is used to evaluate visuospatial memory and working memory. It will be administered as part of the assessment process at baseline (T0) and following training at T1 and T3.NEPSY II—Imitating Hand Positions subtest [46]. This subtest assesses the child’s ability to observe and replicate hand and finger positions demonstrated by the examiner, using both the dominant and non-dominant hand.NEPSY II—Manual Motor Sequences [46]. It involves imitating a series of rhythmic motor sequences using one hand or both.

*Parent-reported questionnaires, which will be administered to a parent or a caregiver:*

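### The primary BoHA comparison at T1 is described without baseline adjustment; it is valid but gives up precision that ANCOVA on the T0 score would recover at almost no cost

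*Protocol article*

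**What the plan says.** The primary outcome is fixed in Section 2.6: "Both Hands Assessment (BoHA [42]), identified as the primary outcome measure". Section 2.1 fixes the time: "T1 will be the primary endpoint aimed at evaluating the short-term effects of AOT". Baseline BoHA will exist for every child, because T0 precedes randomisation (Section 2.1) and Section 2.6 adds: "All tests will be administered at all timepoints, unless otherwise specified". BoHA carries no exception.

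Section 2.8 then sets out a sequence for the clinical outcomes:

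- Baseline: "Initially, differences between the two groups at T0 will be examined for the various outcome variables, assessing the significance of the results" by means of p-values.
- Choice of test: "Depending on the data distribution, parametric or non-parametric tests will be applied".
- Primary comparison: "Subsequently, intergroup differences at the primary endpoint (T1) will be analysed".
- After that, a second level of analysis covers differences between follow-up and baseline. The text does not say whether this is within or between groups.
- Cohen's d with a 95% confidence interval accompanies the results.

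No covariate, change score or longitudinal model is named for the T1 comparison. No model is excluded either. Section 2.3 sizes the trial at 21 per group for a 5-unit BoHA difference (significance level 0.05, power 80%), raised to 27 per group for 20% dropout. It gives no SD, no correlation and no sidedness.

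**The concern.** The baseline score is given two roles, a preliminary significance test and a second-level analysis, and none in the comparison that decides the trial.

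Three things follow. First, variation between children that the T0 score could explain stays in the error term at T1. Eligibility spans ages 5 to 16 and MACS levels I to III, so considerable variation is plausible, and only 54 children are planned. Second, the T0 p-values do not repair this. Under randomisation any T0 difference is due to chance, so the test answers no useful question, and a non-significant result does not show that the imbalance is unimportant. Third, if the choice between a parametric and a rank test also governs T1, the data decide whether the primary result is a difference in BoHA units or a shift in ranks, while the sample size is stated in BoHA units.

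At stake is efficiency, and possibly whether the stated 80% power applies to the comparison described.

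**Working it through.** **Inputs.** From Section 2.3: difference 5 units, 21 per group, alpha 0.05, power 80%, dropout 20%. Assumed, because the documents do not give them: two-sided testing, equal SD at T0 and T1, and the T0–T1 correlation r, shown from 0.3 to 0.9.

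**Step 1: the plan's own figures.** The dropout step reproduces: 21/(1 − 0.20) = 26.25, rounded up to 27. The 21 cannot be checked forward without an SD, so it is solved backwards. A two-sided two-sample t-test (noncentral t) needs 21 per group for 80% power when the SD lies between 5.50 and 5.64. One-sided, the range is 6.24 to 6.40. Below, SD = 5.63 (two-sided). The article does not say whether this is the SD of T1 scores or of change, so both are worked through.

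**Step 2: share of variance removed.** The ANCOVA residual variance is SD²(1 − r²), so the share removed is r²: 9% at r = 0.3, 25% at 0.5, 49% at 0.7, 64% at 0.8, 81% at 0.9. It passes one half only above r ≈ 0.71.

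**Step 3: the implied SD is a T1 SD.** Power at 21 per group uses residual SD 5.63·√(1 − r²) and 2·21 − 3 = 39 degrees of freedom. The n column is the number per group for 80% power.

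| r | residual SD | power | n per group for 80% |
|---|---|---|---|
| unadjusted | 5.63 | 80% | 21 |
| 0.3 | 5.37 | 84% | 20 |
| 0.5 | 4.88 | 90% | 16 |
| 0.7 | 4.02 | 98% | 12 |
| 0.8 | 3.38 | above 99% | 9 |

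**Step 4: the implied SD is an SD of change.** SD(change) = SD(T1)·√(2(1 − r)), so SD(T1) = 5.63/√(2(1 − r)).

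| r | T1 SD | power, T1 comparison | ANCOVA residual SD | power, ANCOVA |
|---|---|---|---|---|
| 0.7 | 7.27 | 59% | 5.19 | 86% |
| 0.8 | 8.90 | 43% | 5.34 | 84% |
| 0.9 | 12.59 | 24% | 5.49 | 82% |

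At r = 0.5 the two readings coincide, since √(2·0.5) = 1. Below 0.5 the T1 SD would be smaller than 5.63, and the T1 comparison would have more than 80% power.

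**Step 5: chance imbalance.** With SD 5.63, the standard error of the T0 difference is 5.63·√(2/21) = 1.74 units at 21 per group and 5.63·√(2/27) = 1.53 at 27 per group. At 27 per group the chance of a T0 gap above 2.5 units (half the target) is P(|Z| > 2.5/1.53) ≈ 10%. Only r times an imbalance carries into an unadjusted T1 difference. At 21 per group, a one-standard-error imbalance shifts the estimate by 0.5·1.74 = 0.9, 0.7·1.74 = 1.2 or 0.9·1.74 = 1.6 units at r = 0.5, 0.7 or 0.9.

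**The case against.** The strongest objection is that this rests partly on silence. The article names no test for the T1 comparison, never calls it unadjusted, and condenses a fuller plan that may list covariates. That stands as far as it goes: a reader might infer that baseline is definitely excluded, and the text does not establish this. But Section 2.8 is not merely silent. It places baseline in a significance test and in a second-level analysis, with the T1 group comparison between them. ANCOVA would be a better method than the one described, not just added detail.

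Three stronger readings are tempting and not supported:

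- **Most of the precision is lost.** This needs r above about 0.71, and the documents give no r. At 0.5 the share is a quarter.
- **The result is biased by baseline imbalance.** Under randomisation, imbalance is random error that the standard error and type I error already cover, and only the fraction r of it carries over.
- **The trial is certainly underpowered.** SDs of 8, 10 or 12 would give unadjusted power of 51%, 35% or 26%, but none of these SDs is in the documents. If the SD implied by 21 per group is a T1 SD, unadjusted power is 80% by construction.

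Two further points have some force. The sentence on test choice directly follows the T0 sentence, so its application to T1 is a plausible reading and not a certain one, and Cohen's d is a mean-based measure. No stated rule makes later analyses depend on the T0 p-values. Finally, the trial is exploratory with feasibility first, which lowers the urgency but does not remove the gain.

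**Conclusion.** The point holds as one of efficiency and prespecification. The primary comparison as described is valid and unbiased, but it leaves unused a baseline score that the trial collects anyway.

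The size of the loss depends on r and on what the planning SD refers to, neither of which is stated. If about 5.6 is a T1 SD, the planned power is met and ANCOVA adds 4 to 18 percentage points for r between 0.3 and 0.7. If it is an SD of change, the T1 comparison falls to 59% power at r = 0.7 and to 24% at r = 0.9, while ANCOVA stays above 80%. Over the correlations shown, ANCOVA keeps the stated 80% under both readings. The T1 comparison does so under the first, but under the second only while r is no higher than about 0.5.

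These figures assume a two-sided test, equal SDs at T0 and T1, and a linear relation between the two scores. The T0 significance tests are stated outright and are uninformative whatever the value of r. This is a worthwhile, inexpensive improvement, not a flaw that invalidates the trial.

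**What to change.** In Section 2.8, before any outcome data are seen by group:

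- Prespecify as the primary analysis an ANCOVA of T1 BoHA on allocated group with T0 BoHA as covariate. Report the adjusted difference in BoHA units with its 95% confidence interval.
- Replace the T0 p-values with a descriptive baseline table.
- State that the observed distribution will not switch the primary analysis to a rank test. If residuals are a worry, bootstrap or permutation inference can be applied to the same adjusted difference.
- In Section 2.3, state the SD behind the 21 per group, whether it is a T1 or a change SD, and whether the test is two-sided.

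Optional: add centre as a covariate, and use the same model for secondary outcomes measured at T0.

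The cost is one paragraph, no new data, and one or two degrees of freedom.

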### 2.2. Participants

Participant recruitment will be conducted by the two clinical centres involved in the project, in accordance with predefined inclusion and exclusion criteria (IRCCS Fondazione Stella Maris and AUSL IRCCS of Reggio Emilia), selected within databases that collect data of subjects who have previously given consent to receive information and proposals for new research protocols, and among patients referring to the above-mentioned structures for functional assessments and/or rehabilitation care. Eligible subjects and their families will subsequently receive invitations to participate in the study, and informed consent will be obtained from the subjects and/or their caregivers before enrolment. Subjects will be recruited based on the following specific inclusion criteria:Confirmed diagnosis of spastic diplegic Cerebral Palsy;Age between 5 and 16 years at the time of recruitment;Manual Ability Classification System (MACS) levels I–III [39];Gross Motor Functional Classification System (GMFCS) levels I–III [40];At least one cognitive functioning index greater than −2 standard deviations, assessed with a battery of standardized tests such as WISC-IV or WISC-V, in order to ensure a sufficient level of comprehension and cooperation in the proposed activities.

Moreover, the following exclusion criteria will be applied:Presence of uncontrolled epilepsy;Injection of botulinum toxin or orthopaedic surgery in the upper limb carried out in the previous 6 months or planned during the study period.

Participants will be removed from the study regardless of their allocation group if any of the following conditions are met:They begin an intensive treatment program;They require a botulinum toxin injection before the end of the study;Other adverse events occur that prevent further participation.

A subgroup of patients from EG and CG will be selected to perform a functional magnetic resonance imaging (fMRI) assessment. For these participants, additional exclusion criteria will be the following:Insufficient cooperation during approximately 30 min long neuroimaging studies;Presence of exclusions for 3T MRI investigations (as metal implants, prostheses, shunts, etc.). These exclusions will be checked using an ad hoc questionnaire.

Moreover, a subgroup of age-matched typically developing (TD) children, recruited on a voluntary basis, will be also enrolled as healthy control group.

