### 2.5. Standard Care

Participants originally allocated to the CG will pursue their usual care for 8 weeks.

Standard care for children with CP in Italy is provided primarily through the Italian National Health Service, which ensures access to care through a network of public and accredited rehabilitation facilities. The model of care is coordinated and multidisciplinary, typically involving professionals in child neuropsychiatry, physiotherapy, childhood neuromotor development therapy, speech and language therapy, psychology, orthopaedics, and social services. Despite the broad availability of services, access and quality of care may vary across regions due to differences in resource allocation, staffing, and waiting times. Moreover, the dose and the content of the standard care are often negligible in having a meaningful impact on the short-term outcome, particularly among adolescents. Due to ethical reasons, it is not possible to ask to interrupt the traditional standard care, and in this sense, the participation in the ACT ON DIP project does not intend to interfere with the traditional care, so no other standard intervention will be forbidden to participants of both groups.

During this period, participants will be asked to wear Actigraphs on both wrists.

Families of children in both groups will be asked to complete a daily diary during the 8-week training period, providing details regarding the frequency, duration, and type of all the main therapies, routines, and activities performed. The diary will have a daily checklist of the most common daily life activities, wake-up and school times. The daily diary will also include a guide on correctly using and managing the given wearable sensors.

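### Section 2.8 names a between-arm comparison only at T1; the medium- and long-term effects of AOT need a stated EG–CG contrast at T2 and T3

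*Protocol article*

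**What the plan says.** Section 2.1 makes T1, after the 8-week period, the primary endpoint for short-term effects. It continues: "All participants will also be evaluated at 8 and 24 weeks (T2 and T3, respectively) after T1", and gives the purpose as "to evaluate the medium- and long-term effects of AOT".

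Section 2.8 sets out the clinical analysis in order. The arms are first compared at T0. Next: "Subsequently, intergroup differences at the primary endpoint (T1) will be analysed". Then, as a separate step: "A second level of analysis will be performed to assess differences between follow-up and baseline evaluations". Cohen's d with 95% confidence intervals is added, without saying for which contrast.

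Two other places bear on the point. Section 2.6 schedules CP QOL and PEM-CY at T0 and T3 only. Section 2.5 describes the control condition as follows: "Participants originally allocated to the CG will pursue their usual care for 8 weeks". It adds that "no other standard intervention will be forbidden to participants of both groups".

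**The concern.** The aim for T2 and T3 is an effect of AOT, which is a difference between randomised arms. The only analysis described beyond T1 is a difference from baseline, and the text does not say that this difference is then compared between arms.

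A change from baseline in one arm contains everything that happens to a child between the two visits. Here that includes up to 32 weeks of development ("Age between 5 and 16 years at the time of recruitment"), familiarity with tests given repeatedly, and continuing usual care. The control arm is assessed at the same visits and carries the same influences, so comparing the arms removes them.

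If the comparison over time is what gets reported, improvement shared by both arms could be presented as a lasting benefit of AOT.

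**Working it through.** **1. What each analysis in Section 2.8 covers**

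- T1: a between-group comparison is named.
- T2 and T3: no between-group comparison is named. The second level is defined against baseline.
- Repeated-measures ANOVA with within-subject and between-group effects: for BOLD signal only. Section 2.7 limits fMRI to T0 and T1, so this cannot cover T2 or T3.
- LASSO step: looks for predictors of change and does not estimate an arm effect.
- CP QOL and PEM-CY have no T1 value (Section 2.6), so the T1 comparison cannot apply to them.

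**2. Length of follow-up**

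T1 is 8 weeks after T0 and T3 is 24 weeks after T1: 8 + 24 = 32 weeks.

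**3. The plan's own sample size (Section 2.3)**

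The inputs are 21 per group, 5 BoHA units, alpha 0.05 and 80% power. No SD and no sidedness are stated, so the 21 cannot be reproduced forwards. It can be solved backwards for the SD with a two-sample t test (40 degrees of freedom, noncentrality (5/SD) × √(21/2)):

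- two-sided: 5/SD = 0.886, so SD = 5.64;
- one-sided: 5/SD = 0.781, so SD = 6.40.

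The dropout step reproduces: 21/(1 − 0.20) = 26.25, rounded up to 27 per group.

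**4. What a test against baseline in EG does when AOT has no effect**

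Paired t test, n = 21, two-sided 0.05, 20 degrees of freedom, critical value 2.086, noncentrality (drift/SD of change) × √21. The drift of 1, 2 or 3 BoHA units, equal in both arms, is assumed.

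The SD of change is also assumed. If 5.64 is the SD at a single visit and r is the correlation between baseline and follow-up, the SD of change is 5.64 × √(2(1 − r)). This gives 3.57 at r = 0.8, 4.37 at r = 0.7 and 5.64 at r = 0.5. The upper end, 6.40, takes the one-sided back-solved value as the SD of change.

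| SD of change | drift 1 | drift 2 | drift 3 |
|---|---|---|---|
| 3.57 | 23% | 69% | 96% |
| 4.37 | 17% | 51% | 85% |
| 5.64 | 12% | 34% | 64% |
| 6.40 | 10.5% | 28% | 53% |

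Worked example: drift 2 and SD 5.64 give 2/5.64 × 4.583 = 1.625, and a significant result in 34% of trials. With no drift the figure is 5%.

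**5. What the arm contrast does**

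If both arms drift by m and AOT adds e, the difference in change is (m + e) − m = e. Shared drift cancels, and with e = 0 the error rate stays at 5% whatever m is. With 21 per group and a 5-unit difference in change, two-sided power is 95% at an SD of change of 4.37, and 80% at 5.64 (the SD already implied by Section 2.3).

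**The case against.** The strongest reply is that the sentence never says within group or separately by arm, and does not name T2 or T3. It can be read as computing change from baseline and then comparing it between EG and CG, which is a common use of change scores. The paragraph opens by describing both arms, and both attend T2 and T3. This is also a condensed article, and a fuller plan may state the contrast. All of that stands, so the text cannot be said to rule out an arm comparison at T2 and T3. It does not fully answer the point: the article goes beyond silence, confining the intergroup analysis to T1 and setting a differently defined step apart for the rest.

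Several stronger readings are tempting and should not be drawn:

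- A reader might infer that a lasting effect will be declared if EG changes significantly and CG does not. No such rule appears in the document.
- A reader might infer that CP QOL and PEM-CY have no randomised comparison at all. That follows only on the plain reading of Section 2.8.
- A reader might add regression to the mean. Section 2.2 sets no BoHA entry threshold, so there is little support for it.
- A reader might fault the design. Both arms are followed to T3; only the stated contrast is at issue.

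On the control condition, the 8-week wording is partly offset. Section 2.5 forbids no standard intervention in either group, and Section 2.2 removes participants who begin an intensive programme whatever their arm. What remains is that the passages should be made consistent.

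**Conclusion.** The point holds as a defect in the stated secondary analysis. On its plain reading, Section 2.8 gives T2 and T3 a comparison over time, which does not isolate the AOT effect that Section 2.1 wants from those visits.

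The percentages in the table are illustrative. They rest on assumed drifts, an assumed SD of change and 21 children analysed, because the document supplies neither drift nor SD. The false-positive rate exceeds 5% throughout the range shown, but its true size is unknown. At r = 0.9 (SD of change 2.52) it would be higher still.

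The trial is exploratory and the T1 primary comparison is untouched. The change should be made, but it does not threaten the main result. If a fuller plan already compares changes between arms, one clause in Section 2.8 settles the matter.

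**What to change.** In Section 2.8, state that the medium- and long-term effects of AOT are the EG–CG differences at T2 and T3, adjusted for the T0 value and reported with 95% confidence intervals, and that within-arm changes from baseline are descriptive.

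A repeated-measures mixed model with baseline value, arm, visit and arm-by-visit would do this, with ANCOVA at T3 for outcomes collected only at T0 and T3. These are examples: a between-arm comparison of change scores would also remove shared drift.

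Separately, reconcile the Section 2.5 description of control care over 8 weeks with the use of T2 and T3 in Section 2.1, so that the reader knows what the later contrast compares.

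The cost is wording. Both arms are already assessed at these visits, so no new data, visits or participants are needed.
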